## Introduction

### Background

Cerebrovascular diseases (CVD) remain a global problem today because of high prevalence and related cognitive impairment. Increase in vascular dementia rate is the current trend worldwide. Thus, the identification of new predictors for CVD seems to be an important medical and social problem. Cerebral small vessel disease (cSVD) is one of the most prevalent forms of CVD. This term is used to describe clinical features and structural changes in brain tissue occurring due to damage of small perforating arterioles as well as capillaries and venules. This vascular pathology results in white tissue and basal ganglia lesion that leads to neurological deficit and cognitive decline (1). cSVD is considered to be the leading cause of cognitive dysfunction and dementia (2–4). Moreover, cSVD is associated with an increasing risk of cerebral infarct and intracranial hemorrhage (5, 6). However, cSVD is a broad term, and it encompasses “pure cSVD,” Binswanger's disease, and mixed dementia (when Alzheimer's disease overlaps with cSVD), which are inherited forms of cSVD (7).

Although there are generally accepted risk factors for cSVD including hypertension, diabetes, and aging (1), recent researches have demonstrated a significant role of sleep disturbances in cSVD progression. The significance of obstructive sleep apnea is now well-established and extensively reported (8, 9). Nevertheless, there is a growing body of literature that recognizes the negative influence of other sleep disorders, including periodic limb movements (LMs) in sleep (PLMS), on the course of cardiovascular diseases and cSVD in particular. A probable explanation of this impact is a sleep fragmentation that results in episodes of heart rate increase and blood pressure elevation (8–12).

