Current evidence suggests that there is repetitive sympathetic activation accompanying PLMS during night sleep. This phenomenon could be a potential link between PLMS and negative impact on the cardiovascular system (36). The presumed cardiovascular effects of PLMS could underlie reported associations of higher PLMI with arterial hypertension severity (48), the incidence of cardiovascular events (49), increased risk of death in patients with systolic dysfunction following acute decompensated heart failure (50), and mortality risk in patients with systolic heart failure (12). It is reasonable to assume that PLMS-related activation of the sympathetic nervous system could be an explanation of the negative role of PLMS in CVD course, although it remains an underinvestigated issue. It is shown in cross-sectional studies that the severity of PLMS is associated with the extent of white matter hyperintensities (WMH) in patients with cSVD (51, 52) and in patients with first-ever minor stroke or transient ischemic attack (53). On the other hand, it is known that any pathological state accompanied by sleep fragmentation (sleep apnea, PLMS, and insomnia) may increase the risk of vascular diseases (9). Therefore, a more general process could be responsible for increased cardiovascular risk in PLMS patients.

Another unresolved question is the relevance of PLMS to cognitive dysfunction. Whereas, PLMS could worsen the course of cSVD, the greater cognitive decline of PLMS patients is expected. However, only a few studies focused on this issue, and their results suggest a positive correlation between the PLMI and cognitive decline. Significant association of higher PLMS frequency with impaired executive function was demonstrated among older men without dementia (54), patients with Parkinson's disease independent from psychomotor speed (55), and patients with cSVD (52). Besides, worse sleep efficiency has been also shown to be associated with poorer performance in tasks evaluating the executive domain (56), but the influence of PLMS on sleep quality and its ability to lead to sleep fragmentation is disputable. Moreover, some authors report that age-related changes in sleep architecture with a decline in slow-wave sleep might mediate age-related decline in executive control (57). It appeared confusing since the prevalence of PLMS increases with age too.

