### The Aim and Objectives

The aim of the study was to define the role of PLMS in cSVD progression and related cognitive decline progression.

The main objectives of the study are:

1) Assessment of the cognitive function in small vessel disease patients at baseline and in the 2-year follow-up.2) Assessment of MRI markers of cSVD at baseline and in the 2-year follow-up.3) Assessment of sleep quality and health-related quality of life in patients with PLMS in comparison with those without PLMS.4) Evaluation of PLMS impact on cSVD progression through constructing multiple regression model.5) Assessment of the association between PLMS and poor sleep quality based on questionnaire data.

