### Statistical Analysis and Sample Size Calculation

The baseline values of MRI scale scores and cognitive tests (listed in Table 1) will be subtracted from the corresponding follow-up values, and percent change from baseline will be calculated. Based on the PLMI (≥15/h or <15/h), two groups will be formed. In order to reproduce results of the cross-sectional study conducted by Kang et al. (51), group comparisons will be made using the Mann–Whitney test for non-parametric statistics or unpaired *t*-test, depending on whether the distribution is normal. To assess the association between the PLMI and total cerebral SVD sum score, as well as WMH volume, Fazekas Scale score, and Scheltens Scale separately, Spearman correlation analysis will be applied. To confirm the data obtained by Leng et al. (54) and complement it with a more detailed cognitive assessment, logistic regression will be utilized to study the association between PLMS and clinically significant changes in cognition from the baseline to the follow-up visit.

Multiple regression analysis will be used to estimate the capability of each of the characteristics of PLMS (LMs, LMI, PLMI, PI, and SILMS index) to predict each of the outcome variables (except for stroke incidence and mortality rate). Adjustment for main predictors of cardiovascular risk (age, hypertension level, body mass index, diabetes mellitus, ischemic heart disease, cholesterol level, and smoking) will be made to determine if the associations are independent of these factors. Comparison of stroke incidence (separately for cerebral infarct, non-traumatic intracranial hemorrhage, and transient ischemic attack) as well as mortality rate due to stroke between two groups will be made using Pearson's chi-square test.

Spearman correlation test will be applied to evaluate the association between the PLMI and scores of self-reported questionnaires (listed in Table 1) and assess the influence of PLMS on sleep quality, mood, and daytime functioning. The level of statistical significance will be set at *p* < 0.05. All statistical analyses will be performed using SPSS version 21.0 (SPSS Inc., Chicago, IL, USA).

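### PLMI is related to the questionnaire scores only by unadjusted Spearman correlation yet read as influence, and the planned covariate adjustment does not clearly reach the visual MRI scales

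*Protocol article*

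**What the plan says.** The Statistical Analysis and Sample Size Calculation section plans two sets of Spearman correlations with PLMI. The first covers the MRI measures: "To assess the association between the PLMI and total cerebral SVD sum score, as well as WMH volume, Fazekas Scale score, and Scheltens Scale separately". The second covers the questionnaires: "Spearman correlation test will be applied to evaluate the association between the PLMI and scores of self-reported questionnaires". The stated purpose of the second set is to "assess the influence of PLMS on sleep quality, mood, and daytime functioning". Neither set names a covariate. Significance is set at p < 0.05 for all analyses.

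Adjustment belongs to a separate block: "Multiple regression analysis will be used to estimate the capability of each of the characteristics of PLMS (LMs, LMI, PLMI, PI, and SILMS index"). That block takes in all outcome variables apart from stroke incidence and mortality. The covariates there are age, hypertension, body mass index, diabetes, ischemic heart disease, cholesterol and smoking. The Discussion adds the baseline level.

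The Outcomes section names total WMH volume change (primary), regional WMH volume change, cognitive change, cerebrovascular events and stroke mortality. It names no questionnaire and no visual MRI scale.

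Two objectives depend on the questionnaires. Objective 3 compares sleep quality and quality of life between patients with and without PLMS. Objective 5 is "Assessment of the association between PLMS and poor sleep quality based on questionnaire data".

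**The concern.** This is an observational study whose groups are formed by PLMI alone, so PLMI may share causes with the scores it is correlated with. The article supplies part of that picture. The Introduction cites "generally accepted risk factors for cSVD including hypertension, diabetes, and aging", says that PLMS become more common with age, and links PLMS to heart failure and alcohol abuse. It also reports age-related change in sleep architecture and then remarks: "It appeared confusing since the prevalence of PLMS increases with age too". The plan accepts the need for adjustment in its regression block but does not carry it to the questionnaires.

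At stake is what can be concluded on objectives 3 and 5. A significant raw correlation would be reported as an influence of PLMS on sleep quality, mood or daytime functioning, although it could partly or wholly reflect age or comorbidity. The same holds for the SVD sum, Fazekas and Scheltens scores if the regression is not meant to cover them.

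**Working it through.** **Step 1. Which analysis covers which variable** (Statistical Analysis section set against Outcomes)

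| Variable | Spearman, no covariates | Adjusted regression |
|---|---|---|
| WMH volume change, total and regional | WMH volume is named; level or change not stated | Yes |
| Cognitive change | Not named | Yes |
| SVD sum, Fazekas, Scheltens | Yes | Unclear: not listed as outcomes |
| Questionnaires | Yes | No |

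Spearman is the only test that names the questionnaires. If the Mann–Whitney or t-test group comparisons are also meant to serve objective 3, they too are unadjusted.

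**Step 2. The plan's own figure.** The sample size is built on the adjusted regression. Assume two-sided α = 0.05, power 80% and conventional effect sizes f² = 0.15 (medium) and 0.02 (small). Then N = (1.960 + 0.842)²/f² + p ≈ 7.849/f² + p, with p = 7.
- Medium: 7.849/0.15 ≈ 52, and 52 + 7 = 59.
- Small: 7.849/0.02 ≈ 392, and 392 + 7 = 399.

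Both stated figures reproduce. The article's group comparison gives a third size, 98.

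**Step 3. Size of a spurious correlation.** The article gives no correlation of age with PLMI or with any score, so these are assumptions. If age is the only link, the induced correlation is r(age, PLMI) × r(age, score):
- 0.1 × 0.2 = 0.02
- 0.2 × 0.2 = 0.04
- 0.3 × 0.3 = 0.09
- 0.4 × 0.4 = 0.16

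**Step 4. False-positive rate.** The simulation used 4000 runs per cell, age uniform over 60–75 years and no PLMI effect. The test was two-sided Spearman at 5%; the article does not state the sides of these tests.

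| r(age, PLMI) / r(age, score) | N = 59 | N = 98 | N = 399 |
|---|---|---|---|
| 0 / 0 | 5.1% | 4.8% | 4.8% |
| 0.1 / 0.2 | 5.4% | 4.9% | 6.8% |
| 0.2 / 0.2 | 6.0% | 6.7% | 12.0% |
| 0.3 / 0.3 | 9.7% | 13.4% | 40.4% |
| 0.4 / 0.4 | 22.6% | 33.9% | 89.1% |

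Age-partial Spearman stayed between 4.4% and 5.7% in every cell run. The simulation error at 5% is √(0.05 × 0.95/4000) ≈ 0.3 percentage points, so those values are consistent with 5%. The induced correlation does not change with N. Only the chance of declaring it significant rises.

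**The case against.** A reader might infer that the whole relation between PLMI and cSVD is tested without adjustment. The document does not support that. Objective 4 makes multiple regression the route to the progression question, the sample size is built on it, and the Discussion adds the baseline level. WMH volume change, the primary outcome, is therefore adjusted for age, vascular risk factors and baseline.

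The visual scales may be covered as well. The sample size text speaks of progression of cSVD features in general and of linear regression, and the analysis section derives percent change for the MRI scales. A broad reading of outcome variables would include them. For these scales the defect is ambiguity, not a demonstrated omission.

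A reader might also infer that the protocol says age drives the questionnaire scores. It does not. It links age to PLMS, to cSVD and to sleep architecture. Confounding of the questionnaire scores is plausible but unstated.

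Other points limit the weight of the concern:
- The 60–75 age range narrows age confounding.
- The exclusions remove sleep apnea, restless legs, psychiatric comorbidity and several sleep- or mood-active drugs.
- The questionnaires are baseline measures and neither primary nor secondary outcomes.
- The abstract concedes that causality cannot be concluded.
- With weak age links the error rate is close to nominal.

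All of this stands, but it does not settle the questionnaire analysis. The article fixes a specific unadjusted test there and gives it a causal purpose, which is more than detail deferred to an analysis plan. The abstract's mention of matched controls does not help either, because the Methods form groups by PLMI alone.

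**Conclusion.** The point holds for the questionnaires. Objectives 3 and 5 rest on tests without covariates, and the stated interpretation is stronger than those tests allow. For the SVD sum, Fazekas and Scheltens scores, the text leaves open whether an adjusted analysis exists. The point does not extend to WMH volume change.

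The size cannot be fixed from the document. It ranges from negligible (about 5–7% false positives at 0.1/0.2) to material (about 10%, 13% and 40% at 0.3/0.3 for 59, 98 and 399 patients). These figures assume that age is the sole shared cause, that PLMS has no effect and that tests are two-sided. The highest rates need 399 patients, a number reached only if the initial 59 show no effect. This is a worthwhile correction to supporting analyses and does not threaten the primary result.

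**What to change.** In the Statistical Analysis section:

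1. Make the inferential test for each questionnaire score, and for the SVD sum, Fazekas and Scheltens scores, an adjusted one: partial Spearman correlation with PLMI, or rank or ordinal regression on PLMI. Use age and the cardiovascular covariates already listed, plus sex, and give a brief reason for the set chosen for sleep and mood scores.
2. Keep the raw Spearman coefficients as description.
3. Replace *influence* with *association* for the questionnaires, which matches objective 5.
4. State whether the visual scales count as outcome variables for the multiple regression.

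The cost is wording and a little extra analysis. The listed covariates are already collected at baseline under the Protocol Outline, and sex is assumed to be recorded routinely. With seven listed covariates plus sex, a partial correlation at 59 patients keeps 59 − 2 − 8 = 49 degrees of freedom, so the adjustment is affordable even at the smallest planned size.

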Since the progression of cSVD features depending on PLMI is the key point of our study and linear regression will be applied, we calculated the sample size (N) based on this type of design. As mentioned above, there are seven independent variables (*p* = 7): age, arterial hypertension level, body mass index, blood sugar level, ischemic heart disease, cholesterol level, and smoking duration, and one tested parameter (PLMI or other parameters of PLMS). The sample size should be calculated depending on effect size: N = 392 + p for small, N = 52 + p for medium, and N = 22 + p for large effect size respectively (104). Thus, for revealing medium effect size, N = 52 + 7 = 59 participants should be enrolled, and for revealing small effect size, N = 392 + p, or 392 + 7 = 399 participants should be enrolled. A large effect size of PLMS is not expected. Therefore, 59 patients should be enrolled initially, and when no effect is revealed, the sample size should be enlarged up to 399. On the other hand, a comparison of cSVD feature prevalence between two groups is also planned as interim analysis. For this purpose, unpaired *t*-test (or Mann–Whitney test, depending on whether the distribution is normal) will be applied, and it requires standard deviation (SD) to calculate the sample size. When SD = 1.22 [obtained by Kang et al. (51)] and given probability for rejecting the null hypothesis α = 0.05, probability of failing to reject the null hypothesis under the alternative hypothesis β = 0.2 and effect size = 0.5, group size *N* = 49 is received when rounded up to the next highest integer. Therefore, at least 49^*^2 = 98 patients should be enrolled, but this number could be changed after another value of SD will be received.

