The reported association between high PLMI and transient sympathetic increase does not clarify whether it is a cause-and-effect connection or these events have the same origin. In this regard, more research using controlled trials is needed to demonstrate the positive impact of prolonged treatment of PLMS on cardiovascular health. The absence of a treated group is also one of the limitations of our study. It could establish the utility of pharmacological reduction PLMS.

Another significant limitation of the proposed study design should be discussed. The baseline level of both cognitive function and WMH volume determinates the speed of further progression of the cSVD. Therefore, the difference between groups at baseline will be the reason for the difference in disease progression. In order to deal with this problem, multiple regression analysis is applied and the baseline level will be included in multiple regression equation. Nevertheless, there is a potential bias related to the eligibility criteria. Only a subgroup of patients with AHI under 5 per hour will be included. Taking into account that the large proportion of cSVD patients has at least mild SOAS, the research will encompass only a small part of cSVD patients. However, we have to exclude even mild SOAS. Obstructive sleep apnea syndrome is accompanied by chronic sleep fragmentation as well as chronic hypoxemia that could worsen cognitive performance. Although the impact of mild SOAS on cognitive performance is still controversial (106–108), we cannot be sure that the presence of this condition will not influence the outcome. Taking into account that LMs in general and PLMS, in particular, could be associated with respiratory events, we would not include patients with even mild OSA with the purpose to avoid the presence of confounding factors.

Notwithstanding these limitations, the results of our study could elucidate the role of PLMS in cSVD progression and provide information about its possible influence on assessed outcomes—cognitive decline progression and MRI changes.

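### The regression sample-size rule is run with p = 7 although the model described has a further baseline term and a tested parameter, so 59 and 399 are one or two patients too low by the plan's own rule

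*Protocol article*

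**What the plan says.** The section Statistical Analysis and Sample Size Calculation gives the rule as "N = 392 + p for small, N = 52 + p for medium, and N = 22 + p for large effect size". It sets p = 7 on the ground that "there are seven independent variables", lists seven cardiovascular risk factors, and continues "and one tested parameter (PLMI or other parameters of PLMS". The results are "N = 52 + 7 = 59 participants should be enrolled" for a medium effect and "392 + 7 = 399 participants should be enrolled" for a small one. Enrolment is to start with 59 and grow to 399 if no effect is seen.

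Earlier in the same section the adjustment set is "age, hypertension level, body mass index, diabetes mellitus, ischemic heart disease, cholesterol level, and smoking", again seven entries and again without a baseline value of the outcome.

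The Discussion, on the limitation that baseline severity drives later progression, gives the remedy: "the baseline level will be included in multiple regression equation".

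**The concern.** In a rule of the form constant + p, the only study-specific input is the number of terms in the model. The article runs the rule with seven terms but describes a regression with more. The baseline level is counted nowhere. The tested PLMS parameter is named beside the seven covariates but is not added to p.

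The baseline term is not incidental, because the Discussion relies on it to handle baseline differences between the groups. At stake is whether two stated sample sizes, the initial one and the enlarged one, belong to the model that will be fitted.

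**Working it through.** **Inputs**
- Constants 52 (medium effect) and 392 (small effect), and p = 7: Statistical Analysis and Sample Size Calculation.
- One tested PLMS parameter: same sentence as p = 7.
- One baseline-level term: Discussion.
- Significance level 0.05: Statistical Analysis and Sample Size Calculation.
- Assumed, because the article does not state them for the regression rule: f² = 0.02, 0.15 and 0.35 for small, medium and large effects, a two-sided test, and 80% power. β = 0.2 is stated only for the two-group comparison.

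**Step 1. Reproduce the stated figures.** With p = 7: 52 + 7 = 59 and 392 + 7 = 399. Both agree exactly, so the addition is right and only the input is in question.

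**Step 2. Count the predictors described.** Seven covariates + one PLMS parameter + one baseline level = 9.

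**Step 3. Apply the rule on each reading of p.**

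| What p counts | p | Medium | Small |
|---|---|---|---|
| As stated | 7 | 59 | 399 |
| Predictors other than the tested one (7 + baseline) | 8 | 60 | 400 |
| All predictors (7 + baseline + tested) | 9 | 61 | 401 |

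The stated sizes return only if the tested parameter is left out of p and the baseline term is dropped from the model.

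**Step 4. Do the constants show which reading is meant?** Under the assumptions above, λ = (z₀.₉₇₅ + z₀.₈₀)² = 7.849. Dividing by f² gives 7.849/0.02 = 392.4, 7.849/0.15 = 52.3 and 7.849/0.35 = 22.4.
- If p counts all predictors, N = λ/f² + p − 1. Subtracting 1 and rounding up gives 392, 52 and 22.
- If p counts only the other predictors, N = λ/f² + p. Rounding to the nearest integer also gives 392, 52 and 22.

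Both readings reproduce the constants, so they do not settle the matter. A one-sided test would give 309, 41 and 17 (subtracting 1 and rounding up), which does not match.

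**Step 5. Effect on power.** This is the power for one coefficient in the nine-predictor model, from the noncentral F with 1 and N − 10 degrees of freedom at level 0.05, under two conventions for the noncentrality.

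| N | f² | Noncentrality f² × (N − 8) | Noncentrality f² × N |
|---|---|---|---|
| 59 | 0.15 | 77.4% | 83.1% |
| 61 | 0.15 | 79.0% | 84.3% |
| 399 | 0.02 | 79.7% | 80.5% |
| 401 | 0.02 | 79.9% | 80.7% |

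The largest gain from two more patients is 79.0 − 77.4 = 1.6 points at the medium effect. At the small effect it is 0.2 points.

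**The case against.** The strongest reply is that the arithmetic is correct and that p = 7 can be read as intended. The article assigns 7 to the adjusters and lists the tested parameter apart, which suits a rule in which p counts only the other predictors. On that reading the model as listed in the statistical section has p = 7, and 59 and 399 are right for it. This stands as far as it goes: the article does not define p, its cited source is not at hand, and the constants fit both readings. A reader might infer that the correct sizes must be 61 and 401; the document does not establish that. The reply does not, however, account for the baseline term, which the Discussion says will be in the equation. With it, even the narrower reading gives 60 and 400.

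A reader might also take the 77.4% at N = 59 to mean that the study is underpowered. That does not follow. With noncentrality f² × N, the stated sizes give 83.1% and 80.5%. With f² × (N − 8), 61 and 401 also stay below 80%, at 79.0% and 79.9%, and 80% is first reached at 63 and 403. Under this stricter convention (noncentrality f² × (degrees of freedom + 2)), 59 patients with only seven predictors in total would also give 79.0%. Part of the shortfall therefore comes from the rule being an approximation.

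Finally, the consequence is slight. The same section asks for at least 98 patients for the two-group comparison, which exceeds 59, 60 and 61 alike. This stands, and it limits the point to a correction of stated figures.

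**Conclusion.** The inconsistency is real and minor. The p used in the rule omits a term that the article promises to fit, and may omit the tested parameter as well. By the plan's own rule the stated sizes are one patient too low (60 and 400) if p excludes the tested parameter, or two too low (61 and 401) if p includes it; the document leaves this open. The effect on power is at most about 1.6 points. No claim is made that 59 or 399 misses 80% power.

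The counts assume one coefficient per covariate and a single baseline term; a categorical covariate with more than two levels would raise p further. The power figures also rest on the inferred effect sizes, two-sided testing and 80% target.

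**What to change.** In Statistical Analysis and Sample Size Calculation, list the baseline level among the regression terms, state whether p includes the tested PLMS parameter, and restate the sizes to match: 60 and 400, or 61 and 401. Alternatively, keep 59 and 399 and report the power they give for the nine-predictor model, naming the effect size and the formula. Either is an edit of a few sentences and adds at most two patients to each figure.

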### Hypothesis

PLMI equal to or more than 15 movements per 1 h of sleep is a predictor of small vessel disease progression.

Null hypothesis: the presence of PLMS with index ≥ 15/h has no influence on cSVD course.

Alternative hypothesis (one sided): the presence of PLMS with index ≥ 15/h worsens cSVD course.

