#### Exclusion Criteria

History of psychiatric comorbidities and substance use disorder—assessed by self-report, clinical history, and the AUDIT.Significant vision loss (leading to difficulties with performing cognitive tasks)—assessed by self-report and clinical history.Presence of dementia—assessed by history and clinical examination.Movement disorders (e.g., tremor, dystonia) that slow down the speed of performing cognitive tasks—assessed by clinical examination.Obstructive sleep apnea syndrome—according to the criteria of International Classification of Sleep Disorders III (14).Restless legs syndrome—according to the criteria of the International Restless Legs Syndrome Study Group (63).Current intake of neuroleptics, benzodiazepines, selective serotonin reuptake inhibitors, and hypnotics—assessed by self-report and clinical history.

Before recruitment, the MDs will explain to each participant the aim and nature of the study, the main steps to be undertaken, the expected duration, the potential risks and benefits and any discomfort it may lead to, voluntary participation, withdrawal from the study at any time, and that withdrawal of consent will not affect his or her subsequent medical assistance and treatment. After eligibility assessment, potential participants will receive an information paper and a consent form. The consent form will be signed before any study procedures begin. The informed consent (IC) is compiled in accordance with the National Standard of the Russian Federation for Clinical investigations and good clinical practice (GOST R ISO 14155-2014) for the creation of IC for information transfer (64). The protocol of the study and the content of the IC have been approved by the local ethics committee of the I.M. Sechenov Moscow Medical University (no. 15-19/25.11.2019). The study has been registered in ClinicalTrials.gov Protocol Registration and Results System (Identifier: NCT04569643 29.09.2020). The scheduled time for patient recruitment is September 2021 to September 2024. This period will be extended if necessary.

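### Testing at 59 patients and enlarging to 399 only if no effect appears, with an undivided p < 0.05, gives a false-positive rate of about 9%, not 5%

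*Protocol article*

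**What the plan says.** All of this is in the protocol article, mostly in Statistical Analysis and Sample Size Calculation.

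- The regression sample size follows a rule of thumb: "N = 392 + p for small, N = 52 + p for medium, and N = 22 + p for large effect size respectively". With seven covariates this gives 59 for a medium effect and 399 for a small one.
- The two sizes are used in sequence: "59 patients should be enrolled initially, and when no effect is revealed, the sample size should be enlarged up to 399".
- One level is given for the analyses: "The level of statistical significance will be set at *p* < 0.05". It is not divided across looks, and no boundary is set for the first look.
- A further look is mentioned: "a comparison of cSVD feature prevalence between two groups is also planned as interim analysis". It is sized at 98 patients (2 × 49) with "α = 0.05, probability of failing to reject the null hypothesis under the alternative hypothesis β = 0.2 and effect size = 0.5".
- The Hypothesis section states a formal null and "Alternative hypothesis (one sided): the presence of PLMS with index ≥ 15/h worsens cSVD course". The significance level itself is not called one- or two-sided.
- The Outcomes section names percent change in total WMH volume as the primary outcome.

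**The concern.** The result at 59 decides whether the study goes on. A positive finding there needs no more patients. A negative one brings in 340 more (399 − 59), and the enlarged sample is tested again. That is a two-stage sequential design, and giving each stage the full 0.05 does not hold the overall error at 0.05.

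Two things are at stake. The headline p-value would not carry its stated error rate. And if the study reports at 59 because the result was significant, the estimate is selected for being large. The Discussion says a positive result could make PLMS a modifiable risk factor for cSVD, so a false or inflated early finding would have consequences.

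**Working it through.** **Inputs.** From the document: N = 59 and 399, p = 7 covariates plus one tested PLMS parameter, level 0.05, interim comparison at 98. Assumed: Cohen's conventional f² = 0.02 (small) and 0.15 (medium), because the article gives only the resulting constants; no effect revealed means p ≥ 0.05; the 59 are part of the 399.

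**1. Reproduce the plan's sizes.** N = (z₀.₉₇₅ + z₀.₈₀)²/f² + p, with (1.960 + 0.842)² = 7.849.
- Small: 7.849/0.02 = 392.4, and 392 + 7 = 399.
- Medium: 7.849/0.15 = 52.3, and 52 + 7 = 59.

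Both match, so the constants imply a two-sided 0.05 test with 80% power. One-sided 0.05 would have given 309 and 41 in place of 392 and 52.

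**2. Overall error with looks at 59 and 399.** Under the null the two test statistics are approximately bivariate normal with correlation √(59/399) = 0.385.
- Two-sided: 1 − P(|Z₁| < 1.96 and |Z₂| < 1.96) = 0.0936. The first look contributes 0.05 and the second adds 0.0436.
- One-sided (1.645 at each look): 0.0910.
- Check: 30,000 simulated regressions with eight predictors and exact t critical values gave 9.2% two-sided and 9.1% one-sided.

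**3. The same with 98 counted as a third test of the same hypothesis.** Two-sided 11.8%, one-sided 11.2%; the simulation agrees.

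**4. What the look at 59 can detect.** Two-sided power from the noncentral F with 1 and 59 − 9 = 50 degrees of freedom and λ = f² × 59.
- Small: λ = 1.18, power 0.187. One-sided power is about 0.28.
- Medium: λ = 8.85, power 0.831.

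**5. Overstatement if the effect is small and the look at 59 is significant.** The statistic is roughly normal with mean √1.18 = 1.086 and must exceed 1.96, a distance of 0.874. Its mean given significance is 1.086 + φ(0.874)/[1 − Φ(0.874)] = 1.086 + 0.2723/0.1911 = 2.51. The ratio to the truth is 2.51/1.086 = 2.3.

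**6. Boundaries that restore 5%** (two-sided, same multivariate normal calculation; power at 399 for f² = 0.02, λ = 7.98, where an undivided 0.05 gives 0.805).

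| Level at 59 | Level at 98 | Level at 399 | Overall error | Power of the 399 test |
|---|---|---|---|---|
| 0.001 | no claim | 0.049 | 4.97% | 0.802 |
| 0.001 | 0.001 | 0.049 | 5.02% | 0.802 |
| 0.026 | no claim | 0.026 | 4.96% | 0.722 |
| 0.026 | 0.026 | 0.026 | 6.4% | not needed |
| 0.026 | 0.05 | 0.026 | 8.2% | not needed |

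**The case against.** **No explicit stopping rule.** The article never defines no effect as p ≥ 0.05 and never says in terms that the study stops and claims success at 59. The same paragraph later asks for at least 98 patients, which fits poorly with a halt at 59. This stands as a caveat, but the size barely moves: if 98 is the floor, looks at 98 and 399 give 9.1% two-sided and 8.8% one-sided. A non-significant test is also the natural reading, because 59 was computed as the size needed to detect a medium effect.

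**Boundaries are often left to a SAP.** True of detail. Here, though, the article itself states a rule for continuing and a single level, and the two together do not control the error. The point rests on what is written.

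**Low power at 59 is intended.** The first stage is sized for a medium effect, where power is about 83%, and 399 exists because 59 cannot show a small one. This is fair. The weak first look is not a separate defect; it matters because a significant result there would end the sequence with an inflated estimate.

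**The study is observational.** It is, and the Discussion calls for controlled trials. It still states a formal null, a directional alternative and one primary outcome, so its p-value should mean what it says.

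A reader might infer two stronger points that the document does not support:
- *That the error is definitely 11–12%.* This counts the 98-patient comparison as a third test of the primary hypothesis. The text describes it as a comparison of cSVD feature prevalence and does not say that it tests percent change in WMH volume or can lead to a claim. The figure applies only if it can.
- *That the staged plan cannot fit the calendar.* The article says "The scheduled time for patient recruitment is September 2021 to September 2024", and two years of follow-up on the first 59 would use most of that window. But the next sentence allows recruitment to be extended if necessary.

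**Conclusion.** The concern holds for the two-stage rule. As written, the chance of a false positive is about 9% (9.4% two-sided, 9.1% one-sided), nearly double the stated 5%. This rests on reading no effect as p ≥ 0.05, on pooling the first 59 into the 399, and on counting one PLMS parameter and one outcome. Testing several parameters and outcomes at 0.05 would add inflation that is not counted here. Whether the 98-patient look adds to it is left open by the text.

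The roughly 2.3-fold overstatement at 59 applies only if the true effect is small. The wording should be corrected before any follow-up outcome data are compared between groups.

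**What to change.** State in the sample-size section which looks can support a claim on the primary hypothesis, whether tests are one- or two-sided, and the level at each look. Any one of these works:

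1. **Strict early boundary (preferred).** Claim an effect at 59, and at 98 if the primary hypothesis is tested there, only at two-sided p < 0.001; test at 399 at p < 0.049. Overall error is about 5.0%, and power at 399 for the small effect is about 80%.
2. **Equal levels.** Use p < 0.026 at both 59 and 399. This holds 5% only if the 98-patient comparison cannot support a claim. Power at 399 for the small effect falls to about 72%.
3. **Descriptive early looks.** Report the results at 59 and 98 without a claim and keep the full 0.05 for 399.

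Whichever is chosen, say whether the 98-patient comparison concerns the primary outcome and what may follow from it.

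The textual cost is one paragraph. The real cost of option 1 is that an early claim becomes rare: by the noncentral F calculation in step 4, with the level set at 0.001, the chance of claiming at 59 is about 1% for the small effect and about 32% for the medium one. Option 3 gives up an early claim altogether. These levels control the error across looks for one parameter and one outcome, not across the several PLMS measures and outcomes.
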